In order to address the second study aim, hierarchical mixed-effect models will be applied to estimate the effects of predictors on the sustainment outcomes. These models will include the fixed effects for all study factors and covariates as well as the random effects for site-level temporal trends. Cohorts of sites will also be controlled to account for differences among funding waves. Fixed effects consist of both static factors, *e.g*., implementation quality during funding period, and time varying factors, *e.g*., external funding support. Correlation analyses among predictors and the variance inflation factors will be used to evaluate the potential multicollinearity in fixed effects. If necessary, a model selection procedure such as backward-elimination regression will be applied to drop some correlated predictors. Statistical significance of a predictor will be tested by Wald’s test (z-test) or the likelihood ratio test (chi-squared test) after fitting the final mixed-effect models. F-tests will also be conducted to test multiple factors simultaneously, *e.g*., external supports received during the implementation period (static) and after the implementation period (time-varying).

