### Estimated sample size and statistical power

We estimate the study will have 64 programs for 3 time points, which means a response rate of roughly 80% at the site level. Assuming this sample size and an intra-class correlation within each site of 0.1, we estimate that the proposed sample size is sufficient to detect an MDE of approximately 0.45 standard deviations between two levels of a dichotomous predictor, *e.g*., the program type. For a continuous predictor, this sample size is sufficient to detect a correlation coefficient of approximately 0.34. These effect sizes are considered small to medium [62]. We expect better power in our analysis, since the mixed-effect models are more powerful than bivariate analysis in the simplified power calculation.

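### Backward elimination is named as the collinearity remedy for Aim 2, and the surviving predictors are then tested as if the final model had been fixed in advance

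*Protocol article*

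**What the plan says.** The Analytic plan of the protocol article handles the second aim in four steps.

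1. It begins with a large model: "These models will include the fixed effects for all study factors and covariates". Random site-level time trends and control for funding cohort are added.
2. Collinearity is assessed by correlations among predictors and by VIF. Neither uses the outcome.
3. The remedy follows: "If necessary, a model selection procedure such as backward-elimination regression will be applied to drop some correlated predictors".
4. Inference comes last. "Statistical significance of a predictor will be tested by" a Wald z-test or "the likelihood ratio test (chi-squared test) after fitting the final mixed-effect models". F-tests are added for several factors jointly.

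The power section assumes "We estimate the study will have 64 programs for 3 time points" and "an intra-class correlation within each site of 0.1", and its calculations are for one predictor at a time. The Aim 2 hypothesis covers three domains (outer context, inner context, intervention characteristics) and gives one example for each.

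**The concern.** The diagnosis and the remedy do not match. VIF describes how the predictors relate to each other. Backward elimination removes the terms with the weakest relation to sustainment, given the others. It can keep two strongly collinear predictors, and it can drop an uncorrelated one. What it reliably does is select on the outcome.

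The survivors are then tested on the same data, with z and chi-squared references that assume the model was chosen without looking at the outcome. If the stay threshold equals the significance level, every retained predictor is significant by construction and the final test carries no further information.

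The likelihood-ratio test adds a separate problem. Comparing models with different fixed effects requires maximum likelihood (ML). With many site-level terms and 64 sites, ML underestimates the variance that static predictors are tested against.

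The answer to Aim 2 is a list of predictors, and the Discussion expects policy and practice recommendations from the study. A list with false entries would carry through to those recommendations.

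**Working it through.** **Inputs**

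- From the power section: 64 programs and 3 time points, so 64 × 3 = 192 site-time records; intra-class correlation (ICC) 0.1.
- Not stated, assumed: two-sided alpha 0.05 and 80% power (1.96 + 0.84 = 2.80).
- Not stated, number of candidate predictors K: Table 2 has 8 constructs, 16 dimension rows and about 36 separately named variables or scales. K = 30 is used as the main case, with 10, 15 and 20 as alternatives.
- Not stated, stay threshold: 0.05 assumed, with 0.10 and 0.157 as alternatives.

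**Step 1. The plan's own figures.** The design effect is 1 + 2 × 0.1 = 1.2, so the effective sample is 192 / 1.2 = 160. For a 50:50 predictor the detectable difference is 2.80 × √(4/160) = 0.443 SD, and 0.452 SD for a 40:60 split. This matches "sufficient to detect an MDE of approximately 0.45 standard deviations between two levels of a dichotomous predictor". For a continuous predictor, tanh(2.80 / √(64 − 3)) = 0.344, which matches "sufficient to detect a correlation coefficient of approximately 0.34". The assumed alpha and power therefore fit the plan. Both figures concern a single predictor with no selection.

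**Step 2. Number of tests alone.** For K independent null tests at 0.05, the chance of at least one false positive is 1 − 0.95^K: 40% for K = 10, 54% for 15, 64% for 20, 78.5% for 30.

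**Step 3. Adding backward elimination.** Simulation with no true effects: 64 sites × 3 waves, random intercept fitted by REML, cohort and time forced in, two thirds of predictors static and one third time-varying, Wald z tests, 500 runs per row, elimination applied in every run.

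| K | Predictor correlation | ICC | Stay rule | Error per predictor, full model | Error per predictor, after elimination | Any false predictor, full model | Any false predictor, after elimination | Mean false predictors after elimination |
|---|---|---|---|---|---|---|---|---|
| 30 | 0 | 0.1 | 0.05 | 5.4% | 7.5% | 74% | 86% | 2.3 |
| 30 | 0.3 | 0.1 | 0.05 | 5.3% | 8.4% | 73% | 84% | 2.5 |
| 30 | 0.6 | 0.1 | 0.05 | 5.3% | 9.3% | 72% | 89% | 2.8 |
| 30 | 0.3 | 0.5 | 0.05 | 6.0% | 8.4% | 79% | 86% | 2.5 |
| 30 | 0.3 | 0.1 | 0.10 | 5.7% | 10.9% | 75% | 96% | 3.3 |
| 30 | 0.3 | 0.1 | 0.157 | 4.9% | 11.4% | 73% | 97% | 3.4 |
| 20 | 0.3 | 0.1 | 0.05 | 5.2% | 7.3% | 61% | 71% | 1.5 |
| 15 | 0.3 | 0.1 | 0.05 | 5.5% | 7.6% | 54% | 61% | 1.1 |
| 10 | 0.3 | 0.1 | 0.05 | 5.7% | 7.1% | 43% | 48% | 0.7 |

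A separate set of runs gave 41–48% for K = 10 and about 59% for K = 15, hence the range of 41–71% for 10 to 20 candidates.

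The direct measure of the fault is the share of retained null predictors with p < 0.05 in the final model. It is 100% at a stay rule of 0.05, 70% at 0.10 and 52% at 0.157.

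**Step 4. ML against REML, no selection.** With 30 predictors and ICC 0.1, error for a static predictor was 12% by likelihood ratio and 10–11% by ML Wald, against 5–6% by REML Wald. With 15 candidates the likelihood-ratio error was 7–10% across ICC 0.1 and 0.5. Averaged over all 30 predictors, the ML Wald error was 10.3% in the full model and 9.9% after elimination. Under ML the bias is thus already present, and elimination adds nothing to it.

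**The case against.** The strongest defence is that the procedure is conditional and illustrative. The article would use selection only if needed, offers backward elimination as an example, and aims it at correlated predictors. The simulation eliminates all terms in every run. In data with 20 static and 10 time-varying predictors correlated at 0.3, the largest VIF had a median of about 3.2, exceeded 5 in 0.5% of runs and never exceeded 10. The article states no cut-off, but at either of those values selection would almost never start on such data. This stands, and it makes the result conditional. It does not clear the method: that check was run only at 0.3, the article itself says the factors do not operate in isolation, and Table 2 lists overlapping measures of support, readiness and attitudes.

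The candidate count is also uncertain. The planned factor analysis may merge items, and the facilitator and barrier data are assigned to Aim 1. This stands, which is why ranges are given.

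A third defence is that most of the familywise error is multiplicity, whose control may sit in an analysis plan that is not shown. This stands too. The point rests on the stated sequence of selection and naive testing, and not on a missing adjustment.

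Finally, the article does not say that the Wald tests use ML, and REML Wald z is close to nominal. That is correct. The ML problem attaches to the likelihood-ratio option, which the article does name.

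**Conclusion.** The point holds as a conditional fault in a stated method. If backward elimination is used, it does not address collinearity, and the named Wald and likelihood-ratio tests on the reduced model are anti-conservative. With 64 sites, 30 null candidates and a 0.05 stay rule, error per predictor is about 1.5 to 1.9 times nominal (7.5/5 to 9.3/5). At least one false predictor appears in about 84–89% of runs, or about 41–71% with 10–20 candidates. The likelihood-ratio test roughly doubles the error for static predictors with about 30 terms, even without selection. All of these figures assume that no predictor has a true effect and that both K and the stay rule are as set here.

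A reader might infer that the study's p-values are invalid in any case and that false predictors are close to certain. The documents do not support that. Selection may never be triggered. The count of 30 is not in the article, and 8 to about 36 is defensible. Rates of 96–97% arise only with 30 candidates and a lenient stay rule. Without selection and under REML, single tests are near 5–6%. Nor can the full 84–89% be charged to elimination, since the same simulated models without it already give 72–79%.

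**What to change.** - **Reduction.** Replace backward elimination with a rule that does not use the outcome: combine overlapping measures into domain scores, or drop terms by a stated VIF limit only.
- **Model.** Fix the Aim 2 model before looking at the sustainment outcome, built around the three domains of the hypothesis. The examples given for each domain are illustrations and need not become the primary predictors. Say where the funding-period implementation variables belong, since the Secondary data section ties a hypothesis to them as well.
- **Tests.** Fit by REML and use Kenward-Roger or Satterthwaite t and F tests in place of the z and likelihood-ratio tests, with one joint F-test per domain. The plan already foresees joint F-tests. Most of the gain comes from leaving ML; the small-sample reference is a refinement, since REML Wald z is already near nominal.
- **Reporting.** Label other single-predictor results exploratory and give confidence intervals.

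Outcome-blind reduction with REML brings the simulated per-predictor error back to about 5–6%. Three joint domain tests at 0.05 would, if independent, give 1 − 0.95³ = 14.3% for any false positive, against 78.5% for 30 single tests. Bonferroni over 30 predictors would hold it at 4.9%, but would raise the detectable effects from about 0.44 to 0.63 SD and from r = 0.34 to about 0.47, so it is not asked for here.

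The cost is analysis wording, slightly wider intervals and fewer predictors declared significant. At submission only the first of three waves had been collected, so at that point the change could precede the longitudinal analysis.

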### Analytic plan

This study involves the use of both qualitative and quantitative analytic methods. The first aim of describing sustainment and the associated innovations, facilitators and barriers will be addressed primarily with qualitative methods. We employ multiple strategies to avoid bias in the analysis and interpretation of the qualitative data by including the use of a multidisciplinary team (rather than a single observer) to collect and analyze the data. In addition, standardized instruments along with semi-structured interview protocols are used to decrease the possibility of bias.

Raw data will be cleaned and descriptive statistics will be conducted at first to check the data quality and integrity for every variable in the raw data. In case of missing information on the quantitative measures, multiple imputation and nonresponse weights will be implemented [59]. All data will be aggregated to the program by time level for subsequent analyses. We recognize that our study design includes data from different time points based on when the organization lost or will lose funding and our proposed data collection period (2013 to 2015). The mixed model can handle these unsynchronized longitudinal measurements so that we can consistently estimate the association between the predictors and the proposed outcomes.

Next, preliminary exploratory analyses will estimate the unadjusted mean trajectories of sustainment outcomes over time among all sites as well as for each site by growth curve models [60] to address the goals of the first study aim. A cluster analysis will [61] identify potential groups of sites where sites in a group will have relatively similar trajectories. If such groups exist, descriptive statistics will be conducted to summarize and compare the mean characteristics of all groups.

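### Collinearity is to be resolved by outcome-driven backward elimination, and the surviving predictors are then tested with ordinary tests that do not hold their nominal level if that step is used

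*Protocol article*

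**What the plan says.** The Analytic plan of the Protocol article sets out a sequence for the second aim.

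1. Starting model: "These models will include the fixed effects for all study factors and covariates as well as the random effects for site-level temporal trends".
2. Diagnosis: "Correlation analyses among predictors and the variance inflation factors will be used to evaluate the potential multicollinearity in fixed effects".
3. Remedy: "If necessary, a model selection procedure such as backward-elimination regression will be applied to drop some correlated predictors".
4. Inference: "Statistical significance of a predictor will be tested by Wald’s test (z-test) or the likelihood ratio test (chi-squared test) after fitting the final mixed-effect models".

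The remedy is conditional, and backward elimination is given as an example. The article states no VIF cut-off, no stay threshold and no allowance for selection in the tests. The power section expects 64 programs at three time points.

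**The concern.** Collinearity is a property of the predictors and can be reduced without looking at the outcome. In the sequence above, the correlations and VIFs decide only whether a reduction is needed. Which predictor goes is then decided by its p-value against sustainment, in the same data that later supply the tests. A predictor that survives has already been favoured for looking associated, and an ordinary Wald or likelihood-ratio test takes no account of that.

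The second aim is framed as a set of hypotheses (Study aims and hypotheses), so these tests carry its conclusions. Overlap among predictors is foreseeable. Implementation-related factors lists clients treated, sessions per client, length of stay and certification counts. The section on perceptions of A-CRA uses compatibility, difficulty and effectiveness items alongside relative-advantage and complexity scales. If selection is used, null predictors can be reported as significant more often than 5% of the time, and a null predictor can stand in for a real one with which it correlates.

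**Working it through.** **The plan's own figure.** The article states no false-positive rate; its figures are detectable effects. Two-sided 0.05 and 80% power are assumed here because neither is stated.

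- Inputs from Estimated sample size and statistical power: 64 programs, 3 time points, "an intra-class correlation within each site of 0.1".
- Effective n = 64 × 3 / (1 + 2 × 0.1) = 192 / 1.2 = 160, or 80 per level at an equal split (assumed).
- Detectable difference = (1.960 + 0.842) × √(2/80) = 0.443 SD, against 0.45 stated; power at 0.45 is 81%.
- Detectable correlation with n = 64: tanh(2.80/√61) = 0.344, against 0.34 stated.

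The figures reproduce, so 64 sites, 3 waves and an intra-class correlation of 0.1 are a fair base for simulation. (The two figures use different effective sizes, 160 and 64; this does not bear on the present point.)

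**Simulation A: blocks of correlated predictors.** 64 sites × 3 waves, intra-class correlation 0.1 treated as known, Wald z tests at 0.05. Assumed, because the article does not give them: 12, 20 or 24 predictors in blocks of four; within-block correlation 0, 0.5 or 0.8; no true effects, or one true predictor per block (coefficient 0.2); stay threshold 0.05, 0.10 or 0.157. The result is the share of null predictors that are retained and significant. Without selection the full model gave 4.6-5.9%.

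| Correlation | True effects | May be dropped | After elimination |
|---|---|---|---|
| 0 | none or one per block | all | 5.6-7.5% |
| 0.5 | none or one per block | all | 5.9-11.3% |
| 0.8 | none | all | 7.8-12.4% |
| 0.8 | none | VIF>2.5 only, stay 0.10 | 9.8-11.6% |
| 0.8 | one per block | all | 14.0-16.0% |
| 0.8 | one per block | VIF>2.5 only, stay 0.10 | 13.6-15.1% |

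In the third row, stay 0.05 gives 7.8-8.5% and stay 0.10 gives 10.1-11.5%. A further run at correlation 0.8 with no true effects, stay 0.10 and dropping limited to VIF>2.5 gave 10.5-13.4%.

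The chance of at least one false positive (20 predictors, no true effects, stay 0.10) rose from 61% to 76% at correlation 0.5, and from 59% to 83% at 0.8.

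**Simulation B: mild collinearity.** 64 sites, pairwise correlation 0.3, no true effects, stay 0.10.

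- Elimination over all 30 predictors: about 5% to about 12%.
- Only predictors above VIF 5 or 10 may be dropped: 4.9-5.3% with 15, 20 or 30 predictors.
- Only predictors above VIF 2.5 may be dropped: 5.1% (15), 5.7% (20), 8.2% (30).

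**What the trigger would catch.** For m equally correlated predictors the population VIF is [1 + (m−2)ρ] / {(1−ρ)[1 + (m−1)ρ]}. With m = 4:

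- ρ = 0.8: 2.6 / (0.2 × 3.4) = 3.8.
- ρ = 0.5: 2.0 / (0.5 × 2.5) = 1.6.

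So the 0.8 blocks are flagged by a VIF cut-off of 2.5, or by inspecting pairwise correlations, which the plan also names. On average they would not be flagged by a VIF cut-off of 5.

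**Checking the remedy.** Outcome-blind pruning at VIF 2.5 (20 predictors, no true effects) gave 5.3-5.4% among retained predictors. With correlation 0.8 and true effects present, however, 29% of the retained null predictors were significant (10% of all null predictors), because a null proxy can replace a dropped true predictor. Blind pruning alone is therefore not enough.

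**The case against.** The strongest reply is that the step is conditional and illustrative. If collinearity is not found, or an outcome-blind procedure is used, there is no inflation. Simulation B supports this: at correlation 0.3, with dropping confined to predictors above VIF 5, the rate stays at 5%. This stands, and it sets the lower end of the range. It does not remove the concern at strong collinearity, where inflation remains even when only flagged predictors may be dropped.

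A reader might infer that false-positive rates roughly double. The article does not support one figure. Across Simulation A the ratio runs from 1.07 to 3.2, depending on assumed inputs. The chance of at least one false positive mostly rises by less than double, and much of it is present without selection; that is multiplicity, a separate matter.

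A reader might also infer that selection is almost certain because Table 2 holds many variables for 64 programs. The stated trigger is collinearity, not a count. Predictor measures already plans exploratory and confirmatory factor analysis, which could consolidate overlapping items beforehand.

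A third inference is that elimination across multiply imputed data sets leaves no single final model. The article says only that "multiple imputation and nonresponse weights will be implemented". How selection and imputation combine is detail that a condensed article can leave to the analysis plan.

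Finally, the hypotheses are worded by domain and joint F-tests are also planned. That softens reliance on single predictors, but F-tests run on a reduced model would face the same selection.

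**Conclusion.** The point holds as a conditional one. The defect lies in a stated method: a procedure driven by the outcome is named as the cure for collinearity, and ordinary tests follow "after fitting the final mixed-effect models". If that step is used, the tests do not hold 5%. With 64 programs the rate per predictor is about 5-16%. It is at or near 5% under mild collinearity with dropping confined to VIF-flagged predictors. At correlations near 0.8 it is about 10-13% with a stay rule of p<0.10 and no true effects, about 8% with a stay rule of p<0.05, and 14-16% when each block contains a true predictor.

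These sizes rest on assumed predictor counts, correlations, effects and stay rules, and on a simplified model without random temporal trends. The direction does not depend on any one of those choices, but the size does.

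**What to change.** Replace the backward-elimination sentence with an outcome-blind rule, for example:

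*Scales that measure nearly the same thing will be combined into a score, or represented by one measure named in advance, using the planned factor analyses and without reference to sustainment data. Distinct hypothesised predictors, such as turnover, trained supervisors and reimbursement, remain as separate terms. All Aim 2 tests and intervals come from this fixed model. Any outcome-driven selection is exploratory, and its p-values are not used as hypothesis tests.*

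The overlapping perception scales are the natural candidates for combining. One score for each Table 2 construct would go too far: organizational type and capacities holds agency type, staffing and turnover together, and merging them would remove predictors that the article expects to matter.

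The change is to wording only. Trial status reports the first wave of data collection complete, so the rule can still be set before the three-wave analysis. The small downside is that near-duplicate scales can no longer be separated.

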### Estimated sample size and statistical power

We estimate the study will have 64 programs for 3 time points, which means a response rate of roughly 80% at the site level. Assuming this sample size and an intra-class correlation within each site of 0.1, we estimate that the proposed sample size is sufficient to detect an MDE of approximately 0.45 standard deviations between two levels of a dichotomous predictor, *e.g*., the program type. For a continuous predictor, this sample size is sufficient to detect a correlation coefficient of approximately 0.34. These effect sizes are considered small to medium [62]. We expect better power in our analysis, since the mixed-effect models are more powerful than bivariate analysis in the simplified power calculation.

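### The two detectable effects in the power statement rest on different effective sample sizes (160 and 64), and the 0.45 SD figure depends on an unsourced ICC of 0.1

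*Protocol article*

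**What the plan says.** All figures are in the Protocol article, Estimated sample size and statistical power. The sample is fixed first: "We estimate the study will have 64 programs for 3 time points". One ICC and the first result, for a two-level predictor with program type as the example, follow together: "an intra-class correlation within each site of 0.1, we estimate that the proposed sample size is sufficient to detect an MDE of approximately 0.45" SD. The second result is for the other kind of predictor: "For a continuous predictor, this sample size is sufficient to detect a correlation coefficient of approximately 0.34". Both are given the same small-to-medium label. The section closes: "We expect better power in our analysis, since the mixed-effect models are more powerful than bivariate analysis in the simplified power calculation".

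Other sections fix what the ICC means here. The Analytic plan aggregates all data to program by time. Primary data places the waves about nine months apart. Study measures (Sustainment) defines the outcome as a program-level sum of eight organizational supports plus treatment fidelity. The Analytic plan enters both static and time-varying predictors. The ICC is therefore the correlation between repeated sustainment scores of the same program.

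**The concern.** One sample and one ICC should give one effective sample size for a predictor that does not change over the waves, and the two detectable effects should then convert into each other. They do not. On a common scale with an equal split, 0.45 SD corresponds to r = 0.22, and r = 0.34 corresponds to 0.72 SD. The text does not say that the basis changes between the two sentences.

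The more favourable figure is also the one that leans on the ICC. A program type does not vary over the waves, so repeated scores add information about it only to the extent that they are weakly correlated. An ICC of 0.1 credits the three waves almost as if they were separate programs, and no source is given for it.

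The second aim is to identify predictors of sustainment. If the ICC is well above 0.1, a non-significant result for a static two-level predictor carries less weight against a 0.45 SD effect than the section implies.

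**Working it through.** **Inputs from the article:** 64 programs, 3 waves, ICC 0.1, 0.45 SD, r = 0.34. **Assumed, because not stated:** two-sided 5%, 80% power, 50:50 split, so z = 1.960 + 0.842 = 2.802.

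**Effective sample size for a static predictor**
- N_eff = 64 × 3 / (1 + 2 × ICC)
- At ICC 0.1: 192 / 1.2 = 160

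**Reproducing 0.45 SD**
- MDE = 2 × 2.802 / √N_eff
- N_eff = 160: 5.604 / 12.649 = 0.443. A t-based version gives 0.446 with 158 df and 0.450 with 62 df. Power at 0.45 SD is 81%. The figure reproduces.
- N = 64: 5.604 / 8 = 0.70. It does not reproduce.

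**Reproducing r = 0.34**
- r = tanh(2.802 / √(N − 3))
- N = 64: tanh(2.802 / 7.810) = 0.344. The figure reproduces.
- N = 160: tanh(2.802 / 12.530) = 0.220. It does not reproduce; power for r = 0.34 would be 99%.

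One-sided testing and 85% or 90% power were also tried. None gives both figures from one N.

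**Common scale (equal split)**
- d to r: 0.45 / √(0.45² + 4) = 0.22
- r to d: 2 × 0.34 / √(1 − 0.34²) = 0.72

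**Sensitivity to the ICC, static predictor.** ICC values above 0.1 are an assumed range. Power at 0.45 SD is Φ(0.45 × √N_eff / 2 − 1.960). For the 75:25 column, MDE = 2.802 / √(N_eff × 0.25 × 0.75); that split is also an assumption.

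| ICC | N_eff | MDE 50:50 (SD) | Power at 0.45 SD | MDE 75:25 (SD) | Detectable r |
|---|---|---|---|---|---|
| 0.1 | 160 | 0.44 | 81% | 0.51 | 0.22 |
| 0.3 | 120 | 0.51 | 69% | 0.59 | 0.25 |
| 0.5 | 96 | 0.57 | 60% | 0.66 | 0.28 |
| 0.7 | 80 | 0.63 | 52% | 0.72 | 0.31 |
| 1 | 64 | 0.70 | 44% | 0.81 | 0.34 |

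The two stated figures sit at opposite ends of this table: 0.45 SD in the first row, r = 0.34 in the last.

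**Response rate.** 64 / 84 = 76%; 80% of 84 would be 67 programs.

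**The case against.** Four counter-arguments deserve weight.

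*Power is not overstated throughout.* A reader might infer from the mismatch that detectability is exaggerated for every program-level predictor. The article does not support that. The correlation of 0.34 gives no credit for repeated waves, so it holds at any ICC, and at ICC 0.1 it understates what the design can detect. Most measures of implementation during funding are counts, averages or proportions, so this conservative figure governs them. This objection stands: the risk is confined to the 0.45 SD figure.

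*An ICC of 0.1 is not shown to be wrong.* It is tempting to call it implausible, since much of the score consists of certified staff, supervision and training processes that could persist over nine months. But the article reports no ICC for this score. Random site-level trends allow for correlation without saying how large it is. The aims anticipate substantial changes after funding ends, and the Background expects staff attrition to impede sustainment. A decline shared by all programs would not lower the ICC once time is modelled, but uneven change would. What can be said is that 0.1 is unjustified and possibly low.

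*The closing sentence is not shown to be false.* One might argue that joint modelling of correlated predictors must cost power. It can, but covariates may also reduce residual variance, time-varying predictors may gain from a higher ICC, and the r = 0.34 calculation leaves the repeated waves unused. The Analytic plan already includes collinearity checks and dropping of correlated predictors. The net direction is uncertain, so the sentence is unsupported rather than wrong. For 0.45 SD, though, the repeated waves cannot be the source of extra power, because they are already counted.

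*Little depends on the calculation.* The set of funded programs is fixed, the first wave is complete, and the section calls its calculation simplified and its figures approximate. That limits the consequence to how results are interpreted. Describing 76% as "which means a response rate of roughly 80% at the site level" is loose rounding and not a substantive error.

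**Conclusion.** The inconsistency holds. Under the assumed two-sided 5%, 80% power and equal split, the section uses an effective sample of 160 for one effect and 64 for the other while presenting both as results of one design. Consistent pairs are 0.44 SD with r = 0.22 at ICC 0.1, or 0.70 SD with r = 0.34 if the repeated waves add nothing.

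The practical weakness is limited to static two-level predictors. There, 0.45 SD is right only if the ICC is about 0.1 and the groups are about equal in size. Over an assumed ICC range of 0.3 to 1 the detectable difference is 0.51 to 0.70 SD, and power at 0.45 SD is 69% down to 44%. These values are conditional on the ICC, which the article neither sources nor estimates. The r = 0.34 figure can stand as a lower bound on what the design offers.

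**What to change.** In Estimated sample size and statistical power:

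1. State alpha, sidedness, power and the assumed group split.
2. Put both effects on the same effective sample size.
3. For static program-level predictors, replace the single pair with a table over ICC 0.1 to 1 (d from 0.44 to 0.70, r from 0.22 to 0.34), with entries for an unbalanced predictor. Give a source for any ICC singled out, and update it with the observed wave-to-wave correlation once the second wave is available.
4. Qualify the closing sentence: 0.45 SD already credits the three waves, and the net effect of joint adjustment on power is uncertain.
5. Optionally, write 76% for 64 of 84.

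The cost is a paragraph and one table. The figure for two-level predictors becomes less favourable at any ICC clearly above 0.1, while the figure for continuous predictors stays the same or improves. No sites, data collection or analyses change.
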